### Multidisciplinary meeting

All patients will be discussed in a weekly, multidisciplinary meeting with vascular surgeons and (intervention)radiologists. Based on the type of pathology and taking in account both the imaging and the mental state, condition, frailty, V-POSSUM and comorbidity of the patient as screened during the MVE visit, consensus will be made concerning the type of treatment these patients will undergo. Regarding revascularization for CLTI there are several options:

Surgical options cover:

- endarterectomy (femoral communal artery) with or without percutaneous transluminal angioplasty (PTA) of any trajectory
- bypass
  - supragenaal, infragenaal, crural

- venous (using the great saphenous vein, small saphenous vein or arm vein) or polytetrafluoroethylene (PTFE)
- aorto-iliacal or femoral.
- may include wound debridement and minor amputation

Endovascular options cover:

- PTA of any trajectory
- with or without a drug eluting balloon
- with or without stenting
- may include wound debridement and minor amputation

Patients treated conservatively and patients requiring primary major amputations are not included in this study.

#### Second visit to the outpatient clinic (treatment)

After treatment planning is complete, the vascular surgeon will discuss this plan with patients and their IC in a second visit to the outpatient clinic. Afterwards both patient and IC are asked to fill in three questionnaires, regarding the SDM process: the CollaboRATE, the ACPS and the PICS (tSDM=0).

#### Clinical admission

At the time of admission, after +/- 2 weeks, a process analysis will be performed by using a process evaluation form designed by the researchers (F1-Vragenlijsten). We will test compliance and evaluate whether the given interventions and/or instructions were performed at home. Patients diaries are used as a guideline throughout this evaluation.

#### SDM Information Brochure

To evaluate the experiences and preferences regarding SDM of patients and their ICs all patients and their ICs are asked to fill in the CollaboRATE, ACPS and the PICS. Specific information brochures concerning the prehabilitation program for patients will be actualized (E3.Informatiemap Prehabilitatie Polikliniek). After three months and at the end of the project the information brochures will be evaluated with patients (if possible) and ICs. Furthermore, an existing patient education video on shared decision making (Divi, Indiveo) will be adjusted for making decisions in CLTI treatment. The video is intended for both patients and ICs. The adjustment of the video will be done in cooperation with patients and ICs.

#### Follow-up at 6 months

At 6 months after revascularization we will again ask patients and their ICs to fill in the WHOQOL-BREF. Patients are also asked to fill in the EQ-5D-5L questionnaire and the iMCQ. The IC is also asked to fill in the CSI. In addition, both patient and IC are asked to fill in an additional questionnaire regarding process evaluation.

### **8.4 Withdrawal of individual research participants**

Participants can leave the study at any time for any reason without any consequences if they wish to do so. Already collected data will be included in the study. Data regarding LOS, mortality, hospital readmission rate and complications will still be collected from the electronic patient dossier (EPD). The investigator can decide to withdraw a participant from the study for urgent medical reasons.

#### **8.4.1 Specific criteria for withdrawal (if applicable)**

Patients will be excluded from the study if they refuse to participate in the prehabilitation program or fill in the questionnaires (with any reason).

Patients will be noted 'lost to follow-up' if they are excluded after revascularization (with any reason). They will not be asked to fill in the questionnaires at 6 months but follow the common follow-up trajectory. All saved content will be kept and used in the study.

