### 3. STUDY DESIGN

An RCT with a cost-effectiveness analysis, will be performed in three non-university large teaching hospitals in the Netherlands (Amphia Hospital Breda, Elisabeth Tweesteden Hospital Tilburg and Meander Medical Center Amersfoort), during the period of November 2025 to May 2028. All patients of 65 years or older, with a new onset of CLTI presented at the outpatient clinic of the vascular surgeon, who are planned for surgical or endovascular revascularization and who meet the in- and exclusion criteria are asked to participate in the study. In addition, their primary IC will also be requested to take part in the study. A primary IC is defined as follows: the person most involved in caring for the CLTI patient and supporting at least one instrumental activity of daily living of the patient or defined as the contact who supports in decisions by the patient. Patients can still be included, if their primary IC refuses participation. However, primary ICs can only be included together with a patient.

At the outpatient clinic information about the POCI-study is provided by a VNP or researcher and patients and ICs receive an information folder. They are called by telephone the next day by a researcher or VNP to ask if they want to participate. If so, oral informed consent will be obtained by the researcher or VNP and patients are randomized immediately upon inclusion, either into the prehabilitation group or the control group, the latter receiving the standard of care. Their IC will automatically be randomized to the same group. Within a few days all patients undergo a general health screening by a VNP or researcher and a blood sample will be taken as part of the standard care. Written informed consent will be obtained during this visit. Afterwards patients receive three questionnaires: the WHOQoL-BREF, the EQ-5D-5L and the iMTA Medical Consumption Questionnaire (iMCQ) (t=0). ICs are also asked to fill in two questionnaires: the WHOQoL-BREF, and the CSI (t=0). Afterwards, patients randomized into the intervention group are referred to the prehabilitation program where they are assessed by a physiotherapist and if indicated also a geriatrician, dietician or a quit smoking coach. The prehabilitation program will take two weeks, considering both the time needed to possibly reach significant results with the program and the time in which treatment is planned and must take place.

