## 5. TREATMENT OF RESEARCH PARTICIPANTS

In this study we will provide a multidisciplinary prehabilitation program to patients that are planned to undergo endovascular or surgical revascularization for CLTI. The duration of the prehabilitation program is at least 2 weeks and consists of seven major components:

- 1) Screening of general health, signs of frailty, comorbidities, nutritional state, and performing functional and cognitive testing, by a vascular nurse practitioner or researcher at the MVE.

All patients included in the study, regardless of control or intervention group, will go through this first step of the MVE. Afterwards the patients in the intervention group start their prehabilitation program, consisting of:

- 2) Screening and provision of personalized, home-based exercises by a physiotherapist. Patients will track their daily activities in a diary.

And, if indicated:

- 3) Provision of nutritional advice by a dietician, based on the body mass index (BMI), Mini Nutritional Assessment Short Form (MNA-SF) score and the SNAQ-score. If indicated, patients will receive high protein nutrient drinks and recommendations of a high protein diet.
- 4) Comprehensive geriatric assessment (CGA) by a geriatrician.
- 5) In case of an iron deficiency anemia (haemoglobin <8,1 mmol/L for male patients and <7,4 mmol/L for female patients), patients will receive iron infusion using ferric carboxymaltose,
- 6) Assessment of self-reliance and home situation by a prearranged homecare nurse
- 7) Guidance and support for smoking cessation by a quit smoking coach.

The IC participates with the patient in the program. We performed a pilot interview study in CLTI patients and their ICs. Their advises and recommendations are incorporated in our prehabilitation program for CLTI and the POCI-study in general.

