### **8.6 Follow-up of research participants withdrawn from treatment**

Subjects withdrawn from treatment will participate in the usual follow-up. LOS, complications, hospital readmission and mortality will be noted.

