## 10. STATISTICAL ANALYSIS

Statistical analyses are performed using IBM SPSS statistical software (SPSS Inc., Chicago, Illinois, USA). A two-sided p-value of less than 0.05 will be considered statistically significant. Adjusted analysis with prognostic baseline characteristics (e.g. gender, age) will be performed using regression analysis. This analysis corrects for baseline differences, optimizes statistical power, and provides better individualized treatment effect estimates. Missing data will be studied for specific patterns of occurrence, and multiply imputed. A power analysis with sample size calculation is performed, as described in paragraph 4.4 (sample size calculation).

Results of categorical data variables are described in frequencies with percentages and differences will be tested using the Chi-square test. Continuous data are described as median (interquartile range) and Mann-Whitney U-tests will be performed to test for group differences. Ordinal variables will be tested using the Mann-Whitney U-test. Data analysis will be done according to the intention-to-treat concept, which implies that all patients are included in the analysis irrespective of whether they completed the prehabilitation program. Secondary, a per protocol analysis will be performed, although interpretability may be difficult for this analysis. All epidemiological issues and statistical methods will be discussed with [name]. [name], a member of the research group.

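### Section 8.4.1 excludes patients who refuse the programme, a post-randomisation ground that in substance only the intervention arm can meet; this conflicts with intention to treat and puts the 6-month questionnaire outcomes at risk

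*Protocol*

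**What the plan says.** **The exclusion.** Section 8.4.1 of the protocol reads: "Patients will be excluded from the study if they refuse to participate in the prehabilitation program or fill in the questionnaires (with any reason". Its next paragraph deals with patients excluded after revascularisation. They are not sent the 6-month questionnaires, and their stored data are kept and used.

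**The order of events.** Section 3 states that "patients are randomized immediately upon inclusion, either into the prehabilitation group or the control group, the latter receiving the standard of care". Section 5 counts the screening visit as the first of seven programme components and adds: "All patients included in the study, regardless of control or intervention group, will go through this first step of the MVE". It then continues: "Afterwards the patients in the intervention group start their prehabilitation program".

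**The analysis set.** Section 10 adopts intention to treat, explained as meaning that "all patients are included in the analysis irrespective of whether they completed the prehabilitation program". A per protocol analysis is secondary. Section 10.2 applies intention to treat to all three economic analyses as well.

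**Data after leaving.** For participants who leave the study, section 8.4 provides for continued collection of LOS, mortality, readmission and complications from the patient record. For those withdrawn from treatment, section 8.6 says: "Subjects withdrawn from treatment will participate in the usual follow-up. LOS, complications, hospital readmission and mortality will be noted". Section 8.5 rules out replacement. Section 10.1 takes LOS from the patient record, not from a questionnaire.

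**The concern.** A patient can refuse the programme only if it is offered, and it is offered only after allocation to the intervention arm. Strictly, a control could decline the shared screening visit, but the other six components can be refused in the intervention arm alone. The first ground in 8.4.1 is therefore a post-randomisation exclusion that depends on allocation. A control with the same reluctance stays in the study because nobody asks.

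Two things are at stake. The first is the 6-month questionnaire data: WHOQoL-BREF, EQ-5D-5L and hence QALYs, iMCQ costs, and the caregiver's WHOQoL-BREF and CSI (caregivers take part only together with a patient, section 3). If exclusion ends their collection, the loss falls more heavily on one arm, and on patients selected by attitude to the programme. The second is the primary analysis set. The protocol uses three terms (leaving the study, withdrawn from treatment, excluded) without linking them, so what happens to refusers' LOS data is left to interpretation in an unblinded trial.

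The second ground, refusing questionnaires, applies to both arms. It is unnecessary for LOS, which needs no questionnaire.

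**Working it through.** **Which outcomes remain for a patient who refuses the programme before revascularisation**

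| Outcome | Collected after exclusion? | Source |
|---|---|---|
| LOS, complications, readmission, mortality | Yes, if 8.4 or 8.6 is taken to cover exclusion | 8.4, 8.6 |
| Baseline questionnaires | Yes; given before referral to the programme, and data already collected are used | 3, 8.4 |
| Hospital costs | No questionnaire needed; taken from financial records | 10.2 |
| 6-month patient and caregiver questionnaires | Not stated; the explicit stop covers only exclusion after revascularisation | 8.4.1 |

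Only the last row has no provision that preserves it. Section 10 offers multiple imputation for missing data. But if every excluded refuser lacks 6-month data, imputation within the intervention arm has to borrow from patients who accepted the programme, and so treats refusers as if they had responded like acceptors with the same baseline.

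The protocol gives no refusal rate. With 300 patients and 1:1 allocation assumed (150 per arm), 10% refusal is 0.10 × 150 = 15 intervention patients and 20% is 0.20 × 150 = 30, plus their caregivers.

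**The protocol's own power figure**

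Inputs from section 4.4: 300 patients, SD of log(LOS) 0.9, LOS ratio 0.75, two-sided alpha 5%, stated power 80%.

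- Log effect = |ln 0.75| = 0.288
- SE = 0.9 × √(1/150 + 1/150) = 0.1039
- Power = Φ(0.288/0.1039 − 1.96) = Φ(0.81) = 79.1%, which agrees with the stated 80%.

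**If refusers were left out of the LOS analysis, without selection**

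SE = 0.9 × √(1/150 + 1/(150(1 − r))), where r is the share of the intervention arm refusing. Power is 76.9% at r = 10% and 74.2% at r = 20%.

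**If refusers were left out and would have stayed longer, with no true effect**

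Let g be the excess mean log(LOS) of refusers over acceptors (assumed). The shift in the intervention mean is −r × g, the spurious LOS ratio is exp(−r × g), and the two-sided error is P(|Z + shift/SE| > 1.96).

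| r | g | Shift | LOS ratio | SE | Two-sided error |
|---|---|---|---|---|---|
| 10% | 0.3 | −0.03 | 0.970 | 0.107 | 5.9% |
| 15% | 0.4 | −0.06 | 0.942 | 0.108 | 8.6% |
| 20% | 0.5 | −0.10 | 0.905 | 0.110 | 14.8% |

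The last shift is 0.10/0.288, about 35% of the targeted log effect. The formula is symmetric: if fitter patients were the ones who decline, g would be negative and the same distortion would run against the programme.

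**The case against.** A reader might infer that the arms necessarily stop being comparable and that the LOS result will be biased. The documents do not support that. Section 8.4.1 sits under the withdrawal heading, where section 8.4 keeps the data already collected and goes on collecting LOS. Section 8.6 says again that "LOS, complications, hospital readmission and mortality will be noted". Withdrawn patients are not replaced, and the only explicit rule on the analysis set is intention to treat. Read together, these provisions favour keeping refusers in the LOS analysis, so the error rates above belong to the less favoured reading. They also rest on assumed refusal rates and on an assumed direction of selection.

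A reader might also infer that all questionnaire and cost data of refusers are lost, and in the intervention arm only. That goes too far. Baseline forms come before referral and are retained, hospital costs come from financial records, and questionnaire refusal can occur in either arm. For refusal before revascularisation, the end of 6-month questionnaires is an inference from exclusion, not a written rule.

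What remains is enough to act on. No section says that patients excluded under 8.4.1 stay in the analysis set, and neither 8.4 nor 8.6 preserves the 6-month questionnaires. Imputation does not repair a loss that depends on accepting the programme.

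**Conclusion.** The point holds as a conflict between 8.4.1 and the intention-to-treat rules in sections 10 and 10.2, created by a post-randomisation ground that in substance only the intervention arm can meet. Bias in the primary LOS analysis is not demonstrated: an intention-to-treat analysis of LOS remains possible and is the more natural reading, though it is not stated.

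The main exposure is the 6-month questionnaire outcomes, which are secondary. If exclusion ends their collection, they are missing more often in the intervention arm, for 15 to 30 patients at an assumed 10% to 20% refusal.

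For LOS, the size is conditional on refusers being left out: a spurious reduction of about 3% to 9.5% and a two-sided error of about 6% to 15%, for 10% to 20% refusal and a log(LOS) excess of 0.3 to 0.5. Without selection, the cost is modest (79.1% to 76.9% power at 10% refusal).

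**What to change.** Remove both exclusion grounds from 8.4.1 and state instead that:

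- refusing the programme is non-adherence, relevant only to the per protocol set;
- refusing a questionnaire is missing data for that questionnaire;
- these patients keep their randomised allocation, stay in the intention-to-treat set for every outcome, and are still invited, with their caregivers, to the 6-month questionnaires unless they decline further contact.

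Leave section 8.4 as it is, both its withdrawal provisions (including withdrawal by the investigator) and the continued collection from the patient record. Limiting exclusion to withdrawal of consent would not be a good substitute: it would overlook the investigator's provision and could be read as dropping leavers whose outcomes 8.4 still collects. Use one set of terms across 8.4, 8.4.1, 8.6 and section 10, so that ending the programme, leaving follow-up and the analysis set are kept apart.

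The cost is an amended paragraph and a few more questionnaires to send, some of which will not come back. Keeping refusers in the analysis may dilute the effect, but section 10 already accepts this by choosing intention to treat. The change should be made early, because 6-month questionnaires that were never sent cannot be recovered.

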### **8.5 Replacement of individual research participants after withdrawal**

Withdrawn subjects will not be replaced.

### **8.6 Follow-up of research participants withdrawn from treatment**

Subjects withdrawn from treatment will participate in the usual follow-up. LOS, complications, hospital readmission and mortality will be noted.

### **8.7 Premature termination of the study**

This study will be terminated prematurely in case of any remarkable negative effects (complications and/or mortality) in the intervention group, compared to the control group.

## 9. SAFETY REPORTING

### 9.1 Temporary halt for reasons of research participant safety

In accordance to section 10, subsection 4, of the WMO, the sponsor will suspend the study if there is sufficient ground that continuation of the study will jeopardise participant health or safety. The sponsor will notify the review committee without undue delay of a temporary halt including the reason for such an action. The study will be suspended pending a further positive decision by the review committee. The investigator will take care that all participants are kept informed.

### 9.2 AEs, SAEs

We want to emphasize that the intervention of this study is already proven safe in CLTI patients (5-7). We don't expect any AE, SAE or SUSARs to take place as a result of this program. The only possibility is an AE or SAE regarding the extra physical activity we ask patients to perform (e.g. when a patient falls and fractures a hip during an extra exercise).

#### 9.2.1 Adverse events (AEs)

Adverse events are defined as any undesirable experience occurring to a participant during the study, whether or not considered related to the prehabilitation program.

All adverse events reported spontaneously by the participant or observed by the investigator or his staff will be recorded.

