#### Multidisciplinary Vascular surgical outpatient clinic for the Elderly (MVE)

Directly after inclusion patients will be referred to the MVE. It is important that the patient brings an informal caregiver, for example a partner, family member or close friend to optimize the (hetero)anamnesis and to make sure all information is understood and processed well. Also, hereby we can investigate the possibility of informal care, provided by friends or family. If needed, home care will already be arranged for after discharge. Written informed consent for participating in the study will be obtained by a researcher or VNP.

- *Vascular surgery Nurse Practitioner or researcher*

A trained VNP or researcher will screen all patients on baseline characteristics, signs of frailty and the presence of risk factors for delirium. Comorbidity will be scored using the V-POSSUM score, ASA-classification, Charlson comorbidity index and the Comprehensive Comorbidity Index (CCI) (Appendix 2-Meetinstrumenten). Frailty will be scored using the Clinical Frailty Scale (CFS) (13) and the Geriatric-8-score (G8-score) (14). The VNP or researcher will withdraw the Mini Mental Status Exam (MMSE) (15) to assess cognitive function. Dietary state is assessed by using the Short Nutritional Assessment Questionnaire (SNAQ-score) (16). Also, an inventory is made of available (informal) care and whether problems are expected after dismissal. Patients randomized to the intervention group, might subsequently be referred to the geriatrician, dietician and a 'quit smoking coach' if necessary.

- *Biochemistry tests*

Biochemistry tests will be performed prior to the visit to the VNP or researcher at the MVE. This will consist of: haemoglobin, haematocrit, MCV, C-Reactive Protein, leukocytes, thrombocytes, liver enzymes (ASAT, ALAT), electrolytes (sodium, potassium, chloride), albumin, MDRD, urea, creatinine, INR, lipid spectrum including cholesterol, vitamin D, vitamin B12, folium acid, transferrin, ferritin. Therefore, three blood tubes will be taken.

- *Physiotherapist*

After the visit to the VNP or researcher, patients in the intervention group will be screened by a physiotherapist. The physical state of the patient will be examined and the following tests are performed:

- Maximal inspiratory and pressure (MIP);
- The 'De Morton Mobility Index' (DEMMI)
- Gripstrength, using the hand dynamometer (JAMAR®);
- Timed Up and Go (TUG) test;
- Timed Chair-Stand test;

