- Gait speed (10 Meter walking test);

Based on these results, patients are provided with their own instructions and home-based exercises (Appendix 2-Meetinstrumenten). Patients are asked to keep track of all their activities in a daily diary.

- *Optional: Geriatrician*

If indicated, patients will undergo a CGA as performed by a geriatrician to assess frailty. Based on the CGA, the geriatrician will, among other things, define preventive measures for functional decline and delirium. Patients will be referred to the geriatrician in case of:

- MMSE < 26
- TUG > 14 sec
- Previous delirium
- Polypharmacy > 4 (cardiovascular risk management medications not included)
- Alcohol consumption > 7 units per week
- G8-score < 14

- *Optional: dietician*

If indicated, a dietician will evaluate the nutritional status of the patient (using the MNA-SF score and the SNAQ-score). If indicated, they will receive high protein nutrient drinks and recommendations of a high protein diet.

- *Optional; quit smoking coach*

If indicated, patients will be referred to a 'quit smoking coach' to receive guidance in reducing nicotine abuse. They will see the patients within 3 days after referral and offer appropriate guidance on an individual basis or group therapy.

- *Optional; iron infusion*

In case of iron deficiency anemia (haemoglobin <8,1 mmol/L for male patients and <7,4 mmol/L for female patients), patients will receive iron infusion using Ferinject (ferric carboxymaltose). This will clinically take place during a day-care admission. Patients will receive a dose of 1000mg intravenous in 15 minutes.

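### Adverse events are recorded only if volunteered or observed, while only the intervention arm has programme contacts and a diary, so non-serious preoperative events are likely to be captured unequally

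*Protocol*

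**What the plan says.** Protocol section 9.2.1 gives two routes by which an adverse event (AE) enters the data: "All adverse events reported spontaneously by the participant or observed by the investigator or his staff will be recorded". The scope is wide and covers both arms: "Adverse events are defined as any undesirable experience occurring to a participant during the study, whether or not considered related to the prehabilitation program". No section prescribes a checklist, a question at a visit, or a search of the electronic patient dossier (EPD) for AEs.

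The arms share the screening at the multidisciplinary clinic for the elderly (MVE). Section 5 says: "All patients included in the study, regardless of control or intervention group, will go through this first step of the MVE". They also share the second visit to the surgeon and the admission (section 8.3).

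Other contacts before revascularisation belong to the programme. Section 8.3 says: "After the visit to the VNP or researcher, patients in the intervention group will be screened by a physiotherapist". It adds: "Patients randomized to the intervention group, might subsequently be referred to the geriatrician, dietician" and the quit smoking coach. Section 5 also lists iron infusion and a homecare nurse, if indicated. On the physiotherapy component, section 8.3 says: "Patients are asked to keep track of all their activities in a daily diary". Of the process evaluation at admission it says: "Patients diaries are used as a guideline throughout this evaluation".

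Section 8.2 states that the trial is not blinded.

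**The concern.** Under passive capture, the chance that an event is recorded depends on how often the patient meets someone who would note it and on what prompts the patient to mention it. Here both differ by arm, by design, in the weeks between randomisation and revascularisation.

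That is also when the intervention is given. Section 9.4 asks the data safety monitoring board (DSMB) to assess the safety of the prehabilitation component. Section 9.2 names a fall during an extra exercise as the kind of harm to expect. A fall that leads to admission will probably reach the hospital record in either arm. A fall at home without admission, or a minor worsening of wound or limb, may not.

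If such events are tabulated by arm, an excess with prehabilitation could reflect fuller capture, and a real excess could be dismissed for the same reason. Section 8.2 offers standardised assessment procedures as the answer to the lack of blinding, but the AE rule in 9.2.1 is not standardised.

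**Working it through.** **1. Opportunities for capture from randomisation to admission**

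| Contact or prompt | Intervention | Control |
|---|---|---|
| MVE screening | all | all |
| Physiotherapist assessment | all | none |
| Geriatrician, dietician, smoking coach, homecare nurse, iron infusion in day care | if indicated | not part of the study |
| Daily activity diary | all | none |
| Second visit to the surgeon | all | all |
| Admission | all, with the diary as guide to the process evaluation | all, no diary |

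No row is larger for controls. The difference can therefore only add recorded events in the intervention arm, unless it is offset by something the protocol does not describe.

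**2. The plan's own figure**

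There is none to reproduce. The protocol gives no AE rate and no capture rate. Section 11.4 says only that little or no AE risk is expected.

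**3. Illustration on assumed inputs**

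- Arm size: 150, from the 300 patients in section 4.4 and an assumed 1:1 allocation (the ratio is not stated).
- True risk *t* of a non-serious preoperative event, equal in both arms: assumed 5% to 30%.
- Capture probability: assumed 90% with prehabilitation and 90%, 75%, 60% or 45% in controls.

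Observed risk = *t* × capture probability. With equal *t*, the apparent risk ratio is the ratio of the capture probabilities, whatever *t* is:

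- 0.90 / 0.75 = 1.2
- 0.90 / 0.60 = 1.5
- 0.90 / 0.45 = 2.0

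The chance of a nominally significant excess with prehabilitation (two-sided 5%, normal approximation) is Φ[(d − 1.96·se0)/se1], where d is the difference in observed risks, se0 the pooled standard error and se1 the unpooled one. For *t* = 10% and capture of 90% vs 60%:

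- observed risks 0.09 and 0.06 (13.5 and 9 expected events), so d = 0.03
- se0 = √(0.075 × 0.925 × 2/150) = 0.0304
- se1 = √[(0.09 × 0.91 + 0.06 × 0.94)/150] = 0.0304
- (0.03 − 0.0596)/0.0304 ≈ −0.975, so the chance is 16.5%

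| True risk | 90 vs 90 | 90 vs 75 | 90 vs 60 | 90 vs 45 |
|---|---|---|---|---|
| 5% | 2.5% | 5.1% | 10.1% | 18.9% |
| 10% | 2.5% | 6.8% | 16.5% | 34.2% |
| 20% | 2.5% | 10.4% | 30.6% | 62.7% |
| 30% | 2.5% | 14.5% | 46.3% | 83.2% |

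The same factor would hide a benefit. A true risk ratio of 0.67 would appear as 0.67 × 1.2 = 0.80, or as 0.67 × 1.5 ≈ 1.0.

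**4. Outcomes that do not rest on this route**

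Section 10.1 takes length of stay from the EPD. Sections 8.4 and 8.6 keep length of stay, mortality, readmission and complications under collection for withdrawn patients, and 8.4 names the EPD as the source. Section 12.1 names the EPD as a data source for the study in general. These outcomes depend little on programme contacts.

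**The case against.** The strongest reply is that no comparison is spoiled, because none is planned. AE rates are not an endpoint in section 8.1, and no between-arm AE analysis is described. The stopping rule in section 8.7 concerns "any remarkable negative effects (complications and/or mortality) in the intervention group, compared to the control group", and DSMB interim review (9.4, 10.4) focuses on complications. This stands. A reader might infer that unequal AE capture distorts the stopping decision or makes the whole safety comparison uninterpretable. The documents do not support that: AE records are not shown to feed those rules, and complications are named as a postoperative outcome in sections 2 and 8.1.2.

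The contact gap is also modest. The only extra visit for every intervention patient is one physiotherapist assessment, held after the MVE visit. The rest is conditional, the programme lasts about two weeks, and both arms then meet the surgeon and are admitted. The protocol does not say whether physiotherapists and other referral staff count as the investigator's staff. This limits the likely size but does not equalise the arms.

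The diary logs activities and serves to check compliance. It is not an AE log, though going through it may prompt a patient to mention a fall. A reader might also infer that staff look for events in one arm only. The text does not say so, and the AE definition covers events regardless of relation to the programme.

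Finally, the capture rates are assumed. At the mildest gap shown, 90% vs 75%, the false-excess chance at 10% risk is 6.8%, not far above the 2.5% with equal capture.

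What remains is that the DSMB must judge a component delivered before surgery, and the stated rule would give it lopsided data on minor preoperative events. A statistical analysis plan could not repair this, since it cannot recover events that were never asked about.

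**Conclusion.** The point holds for non-serious, contact-dependent events between randomisation and revascularisation. As 9.2.1 is written, they are likely to be captured more fully in the intervention arm, and any tabulation of them by arm would be biased towards more events there. The protocol gives neither event rates nor capture rates, so the bias cannot be sized. Ratios of 1.2 to 2.0 follow only from the assumed capture probabilities. Length of stay, mortality, hospitalisations and postoperative complications are largely unaffected. This is a weakness in a data-collection rule that is cheap to correct, and it does not threaten the primary analysis.

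**What to change.** Amend section 9.2.1 along these lines: in both arms the same short set of questions (falls, fractures, unplanned medical contacts, and wound or limb worsening since randomisation) is asked at the second outpatient visit and at admission. The EPD is reviewed in the same way in both arms from randomisation to revascularisation. Any between-arm AE summary uses only these sources. Events known only from programme visits or the diary are still recorded and reported, but listed separately.

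Both contacts already exist in both arms, and neither treatment nor sample size changes. The cost is a few minutes per contact, one eCRF form, the record review, and more non-serious AEs on record.
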